#### Infant eligibility criteria

All liveborn infants born at participating sites before 37 weeks’ gestation for whom active care is planned are eligible for inclusion in the WAMM study. Infants born before 37 weeks’ gestation and not needing immediate resuscitation will be eligible to receive DCC. Infants requiring immediate resuscitation (except at sites who have the facilities to provide resuscitation with intact umbilical cord) are ineligible to receive DCC.

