### Subgroup analyses

Subgroup analyses of DCC60 will be conducted by site, gestational age (<32 weeks vs ≥32 weeks), mode of birth (caesarean vs vaginal) and multiple birth (yes vs no).

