#### Analyses

The primary analysis will be performed at the infant level. For the primary outcome, a linear mixed model will be used, with an identity link, thereby estimating the risk difference in proportions with a 95% CI. The proportion achieving DCC60 in each treatment arm will also be provided. A clustering term will account for the clustering of infants within sites, and a time effect will be incorporated for secular trends. Interactions between the prespecified subgroups and intervention will be incorporated in the main analysis model of the primary outcome of DCC60.

A before-after model will incorporate time and cluster (site) terms to quantify the effect of introduction of data sharing, which commences in the data sharing period (period 1). The sustainability of any increase in DCC60 will be explored in a model incorporating the final period of the study (sustained implementation period) in an extension of the primary analysis model. Further extensions to the primary analysis model will be conducted to explore the treatment effect heterogeneity over time and the secular trends, as detailed in Hemming *et al*.^22^ The details of each local QI programme’s specific interventions may also be explored (eg, inclusion of parent representative) and correlated to DCC60.

Process evaluation outcomes will be summarised using means, medians or proportions as appropriate. These will be shown overall and by cluster groups (groups of up to five sites entering the intervention phase in the same period).

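### Site is the one clustering level named in the primary model although multiples are included; model-based intervals would be slightly too narrow for the primary effect and materially so for the multiple-birth interaction

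*Protocol article*

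**What the plan says.** Under Analyses, the protocol article sets the unit of analysis: "The primary analysis will be performed at the infant level". The model for the primary outcome is also fixed: "a linear mixed model will be used, with an identity link, thereby estimating the risk difference in proportions with a 95% CI". The dependence structure is given in one sentence, which also adds a term for time: "A clustering term will account for the clustering of infants within sites". The before-after model described next likewise equates cluster with site. The variance estimator (model-based or robust) is not stated.

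Infant eligibility criteria begins with "All liveborn infants born at participating sites" and goes on to require birth before 37 weeks and planned active care. Nothing excludes twins or triplets. Subgroup analyses lists multiple birth, yes against no, and Analyses says how it will be tested: "Interactions between the prespecified subgroups and intervention will be incorporated in the main analysis model of the primary outcome of DCC60". The multiple-birth test therefore inherits the dependence structure of the primary model.

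The opening of Statistics calls this text summary information and promises a complete SAP.

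**The concern.** Co-multiples share a mother, a gestation, a delivery team and usually a mode of birth, all plausible drivers of when the cord is clamped. A site intercept with an intra-cluster coefficient of 0.02 (Sample size calculation) cannot represent that similarity. Siblings are also born in the same site and, in practice, the same period, so they have the same treatment state. Their correlation does not cancel out of the treatment contrast; it inflates its variance. A model that treats siblings as independent given site overstates the information in the data and reports intervals that are too narrow. The problem is concentrated in the multiple-birth subgroup, where most infants may have a sibling in the data, and that subgroup is prespecified.

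**Working it through.** **Inputs from the article (Sample size calculation).** Four steps and five periods; 20 sites with about 100 infants per site-period, or 18 sites with about 55; intra-cluster coefficient 0.02; coefficient of variation of cluster size 0.8; 50% to 60%; two-sided 0.05.

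**Assumptions, because the article gives no figures.** Share of infants who are multiples, s = 0.10 to 0.30. Correlation between siblings beyond site, ρ = 0.3 to 0.9. Multiples are treated as complete pairs.

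**Step 1: reproduce the stated power.** Generalised least squares on site-period means, with fixed period effects, a random site intercept and total variance (0.25 + 0.24)/2 = 0.245. Power = Φ(0.10/SE − 1.96).
- 20 × 100, equal sizes: SE 0.0174, power 99.99%. Averaged over gamma-distributed site sizes with coefficient of variation 0.8: 99.99%. Stated: >99%.
- 18 × 55, equal sizes: SE 0.0243, power 98.4%. With coefficient of variation 0.8: about 98%. Stated: >95%.

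Both figures reproduce.

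**Step 2: size of the effect by hand.** For pairs, the residual variance of a mean is multiplied by 1 + ρ among multiples and by 1 + sρ overall. At s = 0.2, ρ = 0.5 the overall factor is 1.10, and √1.10 = 1.049. At the extreme, s = 0.3, ρ = 0.9, it is 1.27, and √1.27 = 1.127.

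**Step 3: planned models.** The model-based SE of the site-only model was compared with its true (sandwich) SE when siblings are correlated, for the main model and for the model with a treatment-by-multiple-birth interaction, with equal site sizes. Coverage = 2Φ(1.96/ratio) − 1; error rate = 1 − coverage. Results for 18 × 55 (SE ratio, coverage of a nominal 95% interval):

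| s | ρ | Primary | Within multiples | Interaction |
|---|---|---|---|---|
| 0.1 | 0.3 | 1.014, 94.7% | 1.120, 92.0% | 1.127, 91.8% |
| 0.1 | 0.9 | 1.041, 94.0% | 1.327, 86.0% | 1.345, 85.5% |
| 0.2 | 0.5 | 1.045, 93.9% | 1.175, 90.5% | 1.183, 90.2% |
| 0.3 | 0.3 | 1.041, 94.0% | 1.103, 92.4% | 1.100, 92.5% |
| 0.3 | 0.9 | 1.118, 92.1% | 1.284, 87.3% | 1.277, 87.5% |

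The 20 × 100 case gives almost the same ratios: primary 1.014 to 1.121, within multiples 1.102 to 1.325, interaction 1.100 to 1.345.

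In the middle row the primary SE goes from 0.0243 to 0.0254, so the 95% half-width goes from 4.8 to 5.0 percentage points (1.96 × SE). The interaction SE goes from 0.0349 to 0.0412, a half-width of 6.8 against 8.1 points.

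**Step 4: power with siblings allowed for (coefficient of variation 0.8).** The best case stays at or above 99.9%. The reduced case falls from about 98.1% to 97.8% (s = 0.1, ρ = 0.3), 97.1% (0.2, 0.5) and about 95.0% (0.3, 0.9).

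**The case against.** The strongest objection is that the text is a summary. It names a site term but does not say that no other term will be used, and it defers to a SAP that is not shown. A reader might infer that the trial has decided to treat siblings as independent; the article does not say that. What remains is that the clustering level was not left open. It is stated, for a stated unit and model, and the interactions are placed in that model. A SAP that follows this text would carry the problem forward.

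Second, intervals are too narrow only under model-based variance. A site-level robust variance would largely absorb the sibling correlation, and the article does not name an estimator. This stands, and it makes the conclusion conditional.

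Third, the size rests on two assumed inputs and on complete pairs. The eligibility criteria require planned active care, and the primary estimand is limited to infants not requiring immediate resuscitation, so a sibling may enter alone. A reader might take the multiples subgroup to consist wholly of sibling sets; the article does not support that. If only a fraction q of multiples have their co-sibling in the analysis, ρ is in effect replaced by qρ. Triplets act the other way, with a factor of 1 + 2ρ for a complete set.

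Fourth, a reader might extend the point to NSCC and the balance measures. The article states no model for those, so there is no stated choice to correct.

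**Conclusion.** The point holds conditionally. Under the structure stated in Analyses, with model-based variance, a multiples share of 10-30% and a sibling correlation of 0.3-0.9 in complete pairs, the true SE exceeds the reported SE by about 1-12% for the primary effect, giving an error rate of about 5-8%. For the effect within multiples and the multiple-birth interaction the excess is about 10-35%, giving an error rate of about 7.5-14.5%. Incomplete pairs reduce these figures.

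The harm is therefore small for the primary result and material for one prespecified subgroup test. Two stronger readings are not supported. The primary result is not seriously compromised: in the middle of the range its interval widens by about 0.2 points on each side. Nor does the sample size justification fail: only the extreme corner brings the reduced case down to about 95%.

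**What to change.** In Analyses, and in the SAP that follows from it, do one of the following for the primary DCC60 model and its subgroup interactions:
- add a second clustering level, for example: *infants are nested within mother (birth event), and mothers within site, each with a random intercept*; or
- keep the site term and state that standard errors use a site-level robust variance with a small-sample correction, which is needed with at most 20 sites.

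Record a sibling link (a common birth-event identifier) for every multiple in the data set. This is easier during the weekly data entry than afterwards.

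The cost is a sentence of analysis text, a small data-linkage task and slightly wider intervals. The sample size need not change.

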### Randomisation

Sites will be randomised at the end of the pre-study period. Randomisation will be performed by minimisation using a computer-generated algorithm, stratified by hospital type (tertiary vs non-tertiary), number of infants expected in the 14-week period and average baseline number of seconds of cord clamping (NSCC) (both as determined during the pre-study period; less than the median vs greater than or equal to the median). Sites will be allocated to commence the quality improvement (QI) programme in period 2, 3, 4 or 5, with the ratio 1:1:1:1 (ie, equal chance of allocation to each period). As there is no sequential order, sites will be randomly selected for the order of randomisation. Only the WAMM statistician and trial manager will be unblinded immediately following randomisation. Allocation will be blinded to sites and other central trial operations staff until 14 weeks prior to the transition period for the allocated step for that cluster group, at which point up to 2–3 essential personnel nominated by the site will be informed to allow for staffing arrangements. All other participating staff at each site will be informed on the first day of the transition period.

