#### Sample size calculation

In hospitals in the Australian Placental Transfusion Study,^23^ DCC60 was achieved in 73% of infants assigned to DCC. The primary hypothesis for WAMM is that implementing the WAMM intervention will increase DCC60 by 10% (eg, from 50% to 60%, or 60% to 70%) adjusted for secular trends (trends over time).

We assumed a (best case) scenario of 10 tertiary hospitals and 10 non-tertiary hospitals, and a birth rate of 5000 per year in the 10 tertiary hospitals and 2500 per year in the 10 non-tertiary hospitals, which yields a total of 75 000 births per 52 weeks, or around 100 000 births in 70 weeks (75 000×14 weeks * 5 periods)/52). Assuming 10% are born <37 weeks’ gestation yields approximately 10 000 preterm births, or ~100 (1000 ÷20 ÷ 5) preterm births at each site within each cluster period of 14 weeks.

Therefore, WAMM will have ~10 000 infants (~100 per cluster per time period), in four steps with up to five clusters per sequence (figure 2), yielding >99% power to detect whether the WAMM intervention results in a 10% improvement in DCC60 (from 50% to 60%) after adjusting for secular trends with a two-sided p value of 0.05, assuming an intra-cluster coefficient of 0.02, and unequal cluster sizes with a coefficient of variation of 0.8. If the number of infants is half of this (5000 total preterm births) over 18 sites (~55 preterm infants within a 14-week period), we still have >95% power to detect a 10% improvement from 50% to 60%, assuming an intra-cluster coefficient of 0.02, and coefficient of variation of 0.8. Given that the variability in a proportion is highest at 50%, any rates higher than this (eg, from 60% to 70%) will have higher power.

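### The primary DCC60 model, as described, carries site and time but no minimisation factor and no infant covariate, which forgoes a small and nearly free gain in precision

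*Protocol article*

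**What the plan says.** Four sections of the protocol article bear on this.

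- **Randomisation.** "Randomisation will be performed by minimisation using a computer-generated algorithm, stratified by hospital type (tertiary vs non-tertiary"), and also by expected number of infants and average baseline NSCC, each split at the median of the pre-study period. All three are fixed characteristics of the site.
- **Subgroup analyses.** DCC60 is to be examined by site, by gestation below or from 32 weeks, and by "mode of birth (caesarean vs vaginal) and multiple birth (yes vs no"). These infant variables must therefore be available.
- **Analyses.** The primary analysis is an infant-level linear mixed model with identity link. It has a clustering term for site, and "a time effect will be incorporated for secular trends". No minimisation factor or infant characteristic is named as an adjuster. A later sentence puts subgroup-by-intervention interactions into the main model.
- **Primary estimand.** The target is one overall risk difference, summarised as a cluster-average effect.

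The Statistics section calls this summary information and promises a complete statistical analysis plan before any analysis.

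**The concern.** Factors used to balance an allocation are normally carried into the analysis, so that the standard error reflects the balance achieved. Here none is named. Baseline NSCC is the pre-study value of the quantity from which DCC60 is derived. Hospital type fixes the gestation range, because non-tertiary sites deliver only from 32 weeks.

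Gestation and multiple birth plausibly predict whether 60 s is reached. The site term removes stable differences between sites, and the time term removes changes shared by all sites. Neither removes a change in case mix at one site from one period to the next. Only four or five sites cross over at each step, so some chance imbalance of this kind is to be expected. Adjustment would take part of it out of the error.

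At stake is precision, together with a clear choice of primary model. Read literally, the interaction sentence makes the intervention coefficient the effect in a reference subgroup, not the overall risk difference. Read as separate subgroup models, it leaves the primary model with no infant covariate.

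**Working it through.** **Inputs from the Sample size calculation section.** The effect is a "10% improvement in DCC60 (from 50% to 60"%), and the test is two-sided at 0.05. Clustering is allowed for by "assuming an intra-cluster coefficient of 0.02". Site sizes are taken to vary, with coefficient of variation 0.8. The design is "in four steps with up to five clusters per sequence". The two scenarios are 20 sites with about 100 infants per site-period, and 18 sites with about 55, each over 5 periods.

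**Assumed, because the document does not give them.** Infant covariates explain 5-10% of within-site variance. The minimisation factors explain 50% of between-site variance, with 90% as an extreme.

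**Step 1: variance components.**
- Total variance = (0.5 × 0.5 + 0.6 × 0.4)/2 = 0.245.
- Between sites: τ² = 0.02 × 0.245 = 0.0049.
- Within sites: σ² = 0.98 × 0.245 = 0.2401.

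**Step 2: reproduce the plan's power.** For site i with mean size mᵢ per period, Vᵢ = (σ²/mᵢ)I + τ²J. With fixed period effects and a treatment indicator in Xᵢ, the variance of the risk difference is the treatment element of (Σ Xᵢ′Vᵢ⁻¹Xᵢ)⁻¹. Site sizes were drawn 400 times from a gamma distribution with coefficient of variation 0.8. Power = Φ(0.10/SE − 1.96), averaged over the draws.
- 20 × 100: SE 0.0177; 0.10/0.0177 − 1.96 = 3.69; power 99.99% (plan: >99%).
- 18 × 55: SE 0.0248; 0.10/0.0248 − 1.96 = 2.07; power 98.1% (plan: >95%).

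Both stated figures reproduce.

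**Step 3: adjust.** Multiply σ² by (1 − R² within) and τ² by (1 − R² between), then recompute.

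| Adjustment | SE falls, 20 × 100 | SE falls, 18 × 55 | Power, 18 × 55 |
|---|---|---|---|
| None | – | – | 98.1% |
| Minimisation factors, 50% explained | 2.0% | 2.8% | 98.5% |
| Minimisation factors, 90% explained (extreme) | 9.6% | 11.1% | 99.5% |
| Infant covariates, R² 5% | 2.4% | 2.4% | 98.5% |
| Infant covariates, R² 10% | 4.9% | 4.8% | 98.8% |
| Infant R² 10% and site 50% | 6.7% | 7.4% | 99.1% |

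The infant rows agree with the shortcut √(1 − R²): √0.95 = 0.975 and √0.90 = 0.949.

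**Step 4: why the site factors add little.** For a site of average size, the sampling variance of its five-period mean is 0.2401/500 = 0.00048 (100 per period) or 0.2401/275 = 0.00087 (55 per period), against τ² = 0.0049. Between-site variance is then 0.0049/0.00538 = 91%, or 0.0049/0.00577 = 85%, of the variance of a site mean. The model therefore relies mainly on within-site contrasts, which fixed site characteristics do not affect.

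**Step 5: size of the case-mix error.** Suppose DCC60 differs by 20 points across the 32-week cut (assumption). Gestation then explains p(1 − p) × 0.20²/0.245 of the variance, where p is the share below 32 weeks. This is 2.6% at p = 0.2 and 4.1% at p = 0.5. Its chance contribution to the estimate has SD = SE × √R²:
- 18 × 55: 2.48 × √0.026 = 0.40 to 2.48 × √0.041 = 0.50 points.
- 20 × 100: 1.77 × √0.026 = 0.29 to 1.77 × √0.041 = 0.36 points.

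This is already part of the standard error.

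**The case against.** **The article is a declared summary.** It lists two terms and excludes none, and a covariate list is often left to the analysis plan. A reader might infer that the model adjusts for site and time only. The text does not say so, and this part of the objection stands. What remains is that the model is described term by term, the allocation factors are absent, and the interaction sentence leaves it unclear which model is primary.

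**Bias.** A reader might also infer that unadjusted case mix biases the result. For example, a 5-point shift in the share below 32 weeks with a 20-point gap in DCC60 gives 0.05 × 20 = 1 point. The documents do not support this as a typical error in the estimate. That sum describes one adjacent-period contrast, whereas the model analyses 90-100 site-periods jointly (18 or 20 sites × 5 periods). Such a shift can hardly arise at non-tertiary sites, which are 8 of the 18 that agreed to take part. Step timing is randomised, so what remains after the site and time terms is chance error. Against the SDs in step 5, one point is about two SDs or more.

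**Power.** A reader might infer that the study is underpowered without covariates. It is not: both figures reproduce unadjusted. Assuming a cluster autocorrelation of 0.8, power in the 18-site scenario is 94.9%, but that reflects the correlation assumption and not the missing covariates.

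**Meaning of the estimate.** With an identity link and no interactions, adjustment leaves the target unchanged if the effect is constant. If the effect varies across subgroups, an adjusted coefficient can weight infants somewhat differently. This caution stands, and it is a reason to report the unadjusted model as well.

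**Conclusion.** The point holds as a modest improvement. As described, the primary model omits the three minimisation factors and every infant-level prognostic covariate, although the site factors are known and gestational age and multiple birth must be available for the subgroups. The loss is about 2-3% of the standard error from the site factors (if half the between-site variance is explained) and about 2.4-5% from infant covariates (R² 5-10%). These R² values are assumptions; the article gives no figure for them. No stated power figure fails and no systematic bias follows. The case for acting is that the change costs almost nothing and settles which model is primary.

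**What to change.** In the analysis plan, define the primary model as the described linear mixed model plus fixed effects for hospital type, expected number of infants, baseline NSCC, gestational age and multiple birth. Keep the model with site and time alone as a sensitivity analysis.

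Leave mode of birth out of the primary model, because the programme might influence it. It can remain a subgroup variable.

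Fit the subgroup-by-intervention interactions in separate models, so that the primary coefficient remains the overall risk difference of the Primary estimand section.

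The cost is wording and a few degrees of freedom at site level: three site-level terms among 18-20 sites. With 5,000-10,000 infants, the infant-level terms cost a negligible amount. No new data are needed, on the inference that the subgroup variables are recorded for all infants.

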#### Data handling and monitoring

All data required for the monitoring and quantitative analysis of the study will be recorded within the electronic data capture system provided. Randomisation and related documentation will be outside the electronic data capture system and stored securely at the University of Sydney. Study-related documentation will be kept in a secure location and held for 15 years after the end of the study or longer, if required, according to local regulation.

Study data will be monitored in accordance with the study’s monitoring plan and using a risk-based approach. It is anticipated that central and remote monitoring will be the primary methods, with onsite monitoring undertaken as required and where indicated by ongoing risk assessment. Monitoring will be performed by the coordinating centre staff or their delegates and will include a centralised review of electronic case report forms and other study documents for protocol compliance, data accuracy and completeness. If required, onsite monitoring visits may involve review of the site file and source data verification, and/or an inspection of facilities. The coordinating centre will be given direct access to source documents and other study-related documents.

### Risk/benefit assessment

There is extremely minimal risk associated with the intervention: DCC has been established as safe and efficacious in both term and preterm infants not requiring immediate resuscitation, and QI programmes are commonplace within hospital practice. The only potential risk identified is the opportunity cost for staff time supporting the WAMM intervention; however, this will be funded as part of the study payments.

### Audit

This study may be subject to audit or inspection by representatives of the coordinating centre and study sponsor (University of Sydney), local or international regulatory bodies, the approving Human Research Ethics Committees (HREC) and local institutions, or as required by law.

